## vii. Pre-Training (To)

Prior to the *training phase*, participants in all groups across all centers will undergo a standardized *functional assessment*, including measurement of clinical outcomes and a gait analysis during which EEG, EMG and kinematics data will be collected. A video of the participants head will be taken to determine the electrode position. In particular, a computer vision algorithms will detect the position of each electrode in 3D in relation to anatomical landmarks. This will allow a standardized 2D cartesian projection that could be shared across centers for statistical analysis. Please note that no video files will be shared, only 2D coordinates will be, which do not contain any personalized information.

### A. Functional assessment

#### *Clinical assessments*

We will assess changes in functional mobility with the standard timed-up-and-go (TUG) test and the 2-minute walk test, balance and fall risk with the MiniBESTest, cognition using the MoCA and CTT, and motor symptoms of PD with the MDS-UPDRS. We will use questionnaires to assess effects on gait self-efficacy (modified gait efficacy scale, mGES and falls efficacy scale international, FES-i), fatigue (FACIT-F) and health-related quality of life (EQ-5D). After the 2-minute walk test self-rated walking quality and mental effort to walk will be assessed using visual analogue scales.

#### *Kinematic and neurophysiological measures*

We will assess preferred gait speed using a 20-m walk test (Primary outcome).

Participants start walking on the treadmill for 7 minutes for familiarization. After that, they will then walk at a fixed speed of 1.4 km/h for 5 minutes, to assess the secondary outcomes, step-width and stride-time and the variance of these parameters, from data of at least 100 strides. The fixed 1.4 km/h is attainable for an estimated 95% of patients with moderate PD. However, for those who cannot attain 1.4 km/h at To, their preferred walking speed To will be their fixed speed during all functional assessments. The treadmill assessment will be repeated at their preferred speed. Additionally, during Treadmill walking data from the EEG and EMG will be collected to derive beta-band power in motor areas and calculate cortico-muscular coherence (CMC) between brain and muscle activity.

## B. Home assessment

A home assessment visit for the period of at least 7 days should be completed. Participants will wear inertial measurement units (IMUs), either a single unit on the lower back or, in a subgroup, a three-sensor system, to continuously record motion data. The sensor on the lower back will be attached using medical tape, while the ankle sensors will be fastened using a self-adjustable band to ensure participant comfort. The sensors can be removed quickly and can be easily repositioned following the instructions provided. The planned number of participants to wear the 3-sensor setup at each site for each interventions follows:

- i. 20 people from SDTT (5 each from Sydney, Kiel, Bologna and Tel Aviv)
- ii. 16 people from SDTT + VR (8 each from Bologna and Tel Aviv)
- iii. 8 people from SDTT + MP (Kiel)
- iv. 8 people from SDTT + VR + MP (Sydney)

Participants will be chosen in order of participation until the minimum sample size required is reached.

Participants will be asked to complete a daily diary via their personal smartphone or by paper pencil depending on their preference, including the following information: medication intake, physical activities performed, freezing of gait (FOG) episodes, falls experienced and information on fatigue. Other than the clinical assessment, that is performed during ON medication, the home assessment contains periods of ON, OFF, and transitions between phases, along with various contextual factors that influence mobility. To accurately evaluate the relationship between improvements in lab-based and daily-life gait outcomes, this diary records the influence of Parkinson's medication and physical activity on mobility during the home assessment and ensures with that comparability between the gait outcomes of T0 and T1. During the functional assessment, participants receive support in personalizing the diary by entering their medication schedule and adding typical physical activities. Over seven days, the diary is completed daily and is expected to take 1–3 minutes per day. Only deviations from the medication schedule need to be noted, while normal intake can simply be checked off for each day. Physical activities, FOG episodes, and falls can be logged by adding abbreviations/X marks in the provided timetable. Participants are encouraged to keep the diary beside their medication box to help prevent late entries, while no daily reminders will be sent to minimize the burden on participants.

## C. Randomization procedures

To ensure that groups between SDTT and SDTT+ do not differ in Kiel and Sydney, a block wise randomization will be employed. Block size of 5 participants will be used to control for age, and H&Y stage. Randomization is done using a standard algorithm implemented in the Python Package NumPy (see here for details: <https://arxiv.org/abs/1805.10941>).

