## 5. The StepuP trial design

### i. Study design

StepuP is a multicenter non-pharmacological randomized controlled trial (RCT) conducted at four clinical centers: Christian-Albrechts-Universität zu Kiel (Kiel), Tel Aviv Sourasky Medical Center (Tel Aviv), University of New South Wales (Sydney), IRCCS Istituto delle Scienze Neurologiche di Bologna (Bologna). 42 PwPD will be enrolled and will be randomized into an intervention group (IG) and a control group (CG) at the clinical sites in Kiel and Sydney. 21 PwPD will be enrolled in Tel Aviv and Bologna and randomized as well into an IG and CG. All Participants will receive a 2-6 week speed-dependent treadmill training (SDTT) aimed at improving gait. Subjects in the IG will receive the same STDD with additional perturbations (SDTT+). Baseline (To) and follow-up (T1 & T2) visits include descriptive, clinical, kinematic and neurophysiological assessment. A 7-day home monitoring with digital sensors will be performed before To and after T2. In Sydney half of the patients in the CG and half of the patients in the IG will have also a second baseline measurement before receiving the SDTT.

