## 6. Statistics and analysis plan

### i. Sample size calculation

The sample size was calculated using the SampSize applicationon for the clinical primary objective (i.e., comfortable gait speed overground, measured in m/sec from a 20 meters walking test), with a significance level (alpha) of 0.05 and power (1-beta) of 0.80, with an allocation ratio of 1:1 in parallel groups. From the available literature, it is known that standard treadmill (SDTT) may improve comfortable overground gait speed up to 0.1 m/sec (from a baseline of 1.26 m/sec) in comparison to standard overground walking and that SDTT with perturbations (SDTT+) may further increase comfortable overground gait speed up to +0.08 m/sec in comparison to SDTT. Thus, we will assume that SDDT+ is superior to SDTT at improving comfortable overground gait speed based on an expected average difference in gait speed between the two groups of +0.08 m/sec with a SD of 0.08 Under this assumption, 17 subjects per group are expected to be enrolled, rising to 20.4 considering a maximum drop-out rate of 20%. This would lead to 41 subjects per trial, rounded to 42 to allow for groups of equal size.

Overall, 126 patients at all clinical sites will in enrolled over a period of 24 months. The recruitment totals for each site is outlined in Table 2. Given the time frame of the trial, recruitment will be monitored on a monthly basis. Should any site encounter recruitment difficulties, other sites have the capacity to recruit additional participants for each cohort as well as to recruit additional cohorts if necessary.

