**Analysis technique:**

Linear mixed effect models with the interaction of treatment and time in the model and a random intercept for participant (Twisk et al., 2018), controlling for relevant potential confounders (e.g., age, H&Y stage). For the EEG data, we will use cluster-based permutation tests time locked to the gait cycle.

viii. Mechanisms underlying changes in gait performance (3b)

**Population:** 126 PD patients

Associations between clinical outcomes and feedback control

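### Blocks of 5 cannot guarantee the planned 1:1 allocation, do not by themselves control age or H&Y stage, and are specified for only two of the four randomising centres

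*Protocol*

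**What the plan says.** Section 5.vii.C (Randomization procedures) is short. It opens with the aim and the centres concerned: "To ensure that groups between SDTT and SDTT+ do not differ in Kiel and Sydney, a block wise randomization will be employed". It then fixes the block and its purpose: "Block size of 5 participants will be used to control for age, and H&Y stage". The tool is named next: "Randomization is done using a standard algorithm implemented in the Python Package NumPy". The section gives no strata, age bands, minimisation rule or composition of a block.

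Three other places bear on it:

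- Section 6.i (Sample size calculation) sizes each trial "with a significance level (alpha) of 0.05 and power (1-beta) of 0.80, with an allocation ratio of 1:1 in parallel groups" and rounds the total to 42 so that the groups are equal.
- Table 2 in section 5.viii.A plans 21:21 in Kiel, 21:21 in Sydney, 11:10 in Bologna and 10:11 in Tel Aviv.
- Section 5.i (Study design) says the Kiel and Sydney patients "will be randomized into an intervention group (IG) and a control group (CG) at the clinical sites in Kiel and Sydney", and then adds: "21 PwPD will be enrolled in Tel Aviv and Bologna and randomized as well into an IG and CG". Table 2 shows that this means 21 at each of the latter two centres.

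Age and H&Y stage otherwise appear as example covariates in the mixed models of sections 6.vi (2a) and 6.vii (3a).

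**The concern.** The randomisation paragraph conflicts with the rest of the protocol in three ways.

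1. **Odd block, two equal arms.** An odd number cannot be halved, so no complete block meets the 1:1 ratio used for the sample size.
2. **Purpose not met.** Permuted blocks in order of entry keep arm counts close over time. They balance age or H&Y only if a separate list runs in each age or H&Y stratum, or if a covariate-adaptive method is used. Neither is described.
3. **Coverage.** The blocking is written for two centres, while four randomise.

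At stake are the planned group sizes, a claim of covariate balance that the procedure does not support, and whether the allocation can be reproduced. The paragraph does not say which arm gets the third place in a block, nor how blocking works in Bologna and Tel Aviv.

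**Working it through.** **Inputs.** Block size 5 and centres Kiel and Sydney (section 5.vii.C). Ratio 1:1, alpha 0.05, power 0.80, difference 0.08 m/sec, SD 0.08, drop-out 20%, 42 per trial (section 6.i). Group sizes by centre (Table 2). The protocol does not state whether alpha is one- or two-sided; two-sided is assumed.

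**The plan's own figure.** The standardised difference is 0.08/0.08 = 1. A two-sample t-test has power 0.781 at 16 per group and 0.807 at 17, so 17 per group reproduces. Then 17 × 1.2 = 20.4, and 2 × 20.4 = 40.8, which gives 41, rounded to 42 (21:21).

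**Split of 42 patients in blocks of 5.** 42 = 8 × 5 + 2, so there are eight complete blocks and the first two places of a ninth. The protocol does not give the block composition, so both readings are shown.

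*Reading A: the majority arm is drawn at random in each block.* Let X be the number of the eight complete blocks with three SDTT+ places, X ~ Binomial(8, ½). After 40 patients the SDTT+ arm holds 16 + X. The last two patients add Y:

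- from a block with three SDTT+ places, P(Y = 0, 1, 2) = 1/10, 6/10, 3/10
- from a block with two SDTT+ places, P(Y = 0, 1, 2) = 3/10, 6/10, 1/10
- averaged, P(Y = 0, 1, 2) = 0.2, 0.6, 0.2

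P(21:21) = P(X + Y = 5) = (0.2 × 56 + 0.6 × 70 + 0.2 × 56)/256 = 64.4/256 = 0.252.

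P(20 in SDTT+) = P(X + Y = 4) = (0.2 × 70 + 0.6 × 56 + 0.2 × 28)/256 = 53.2/256 = 0.208, and by symmetry the same for 22.

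P(gap of 4 or more) = 1 − 0.252 − 2 × 0.208 ≈ 0.33. The arm total can range from 16 to 26, and its mean is 21.

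*Reading B: every block is 3:2 in favour of the same arm.* Eight blocks give 24:16, and the last two patients add 0, 1 or 2 to the larger arm with probability 0.1, 0.6, 0.3. The split is 24:18 (10%), 25:17 (60%) or 26:16 (30%), and never 21:21.

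**The same rule at a 21-patient centre, if it were extended there.** 21 = 4 × 5 + 1. Under reading A, 11:10 or 10:11 occurs with probability 0.625. Under reading B the split is 12:9 or 13:8, so neither planned split occurs.

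**Power** (two-sample t-test, standardised difference 1, two-sided 0.05):

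| Split of 42 | Before loss | After 20% loss |
|---|---|---|
| 21:21 | 88.5% | 80.2% (16.8 vs 16.8) |
| 25:17 | 87.4% | 78.8% (20 vs 13.6) |
| 26:16 | 86.7% | 77.9% (20.8 vs 12.8) |

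**Covariates.** No arithmetic is needed: the section names no strata, so nothing in the procedure links the allocation to age or H&Y. As an illustration, assume a binary factor present in exactly 21 of 42 patients and an unstratified 21:21 allocation. The hypergeometric probability of 13 vs 8 or worse is then 0.217. This is the ordinary chance imbalance of an unstratified trial and is not a bias.

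**Coverage.** Section 5.vii.C covers 42 + 42 = 84 patients. Bologna and Tel Aviv contribute 21 + 21 = 42 of 126, one third.

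**The case against.** **Allocation can still be 1:1.** The protocol does not fix a 3:2 composition. Under reading A the ratio is 1:1 in expectation, and 21:21 is the single most likely split. This stands: a reader might infer that the trial cannot deliver 1:1 at all, but that is true only of each complete block and of reading B.

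**The harm to power is slight.** This stands. At 25:17 the loss is 80.2 − 78.8 = 1.4 points, and a reader who infers an underpowered trial goes beyond the figures.

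**Age and H&Y are handled in the analysis.** Sections 6.vi and 6.vii both name them as example covariates. Adjustment deals with much of the consequence of chance imbalance, but it does not make the statement about the blocks true.

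**The other two centres are not left without randomisation.** Section 5.i says their patients are randomised, Table 2 gives their planned splits, and the sentence on the software is not limited by centre. What is missing is the blocking rule for those centres.

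**Guessable allocations.** A fixed odd block might suggest that late places in a block can be predicted. That requires staff to know earlier allocations and block starts, which the protocol does not say they do. Section 5.xiv puts T0 data collection before assignment and blinds the clinical assessors at T1 and T2. The point is secondary.

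**Centre in the models.** One might also ask for centre to be added throughout. The 2a model already nests participant within centre. The 3a model has only "a random intercept for participant", but its section defines no population, so a centre term matters there only if the Bologna and Tel Aviv VR comparison is pooled under 3a.

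**Conclusion.** The randomisation paragraph is wrong as written and should be corrected.

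- A block of 5 is incompatible with 1:1 in every complete block, so the planned 21:21 is not guaranteed. It occurs in about 25% of sequences under a random majority arm, with a gap of 4 or more in about 33%, and never under a constant 3:2.
- Control of age and H&Y stage does not follow from blocking without strata.
- The blocking is specified for two of four randomising centres and leaves 42 of 126 patients without a stated rule.

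The consequence lies in balance and in the reproducibility of the allocation. The effect on power is about 1.4 points at a 25:17 split. The split probabilities rest on the two assumed block compositions. The power figures assume a two-sided test and equal 20% loss in both arms.

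**What to change.** Rewrite section 5.vii.C to state 1:1 randomisation within each of the four centres, in permuted blocks of even size, preferably varying at random. Then choose one of two options:

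- stratify the lists by a coarse H&Y split, or
- delete the claim that blocking controls age and H&Y stage.

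In either case, make age and H&Y stage fixed, named covariates in the 2a and 3a models instead of examples. No centre term needs adding to 2a. Add one to 3a only if Bologna and Tel Aviv are pooled there.

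The cost is an edit to the allocation script and a protocol amendment, with no extra patients or visits. One small downside is that incomplete blocks within strata can leave a difference of a few patients. With blocks of at most 4 the difference is at most 2 per stratum, so at most 4 in a centre with two H&Y strata. If recruitment has begun, apply the new rule to the remaining allocations.

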### viii. Intervention and control

## A. General description

All subjects will receive Speed-Dependent Treadmill Training (SDTT) as a basic intervention. To understand the effects of different kinds of perturbations, each center will do SDTT + additional perturbations. Tel Aviv and Bologna will apply virtual reality (VR) based perturbations, Kiel and Sydney will administer motor perturbations, as shown in Table 2. Intervention and Control groups.

Each intervention program will comprise 12 sessions of 30 minutes each, with a 5-minute warmup and cool down at comfortable overground speed. The comfortable (CS) overground speeds will be determined before each training session using a 20-meter walk test.

**Table 2. Intervention and Control groups.**

| Center   | Intervention Group |    | Control Group                   |    | Treadmill sessions |
|----------|--------------------|----|---------------------------------|----|--------------------|
|          | Treatment          | N  | Treatment                       | N  |                    |
| Bologna  | SDTT+VR            | 11 | SDTT                            | 10 | 12                 |
| Kiel     | SDTT+APP           | 21 | SDTT                            | 21 | 12                 |
| Sydney   | SDTT+VR+APP        | 21 | SDTT (2 nd baseline) | 21 | 12                 |
| Tel Aviv | SDTT+VR            | 10 | SDTT                            | 11 | 12                 |

SDTT: Speed-Dependent Treadmill Training; SDTT+VR, SDTT with virtual reality; SDTT+APP, SDTT with anteroposterior perturbations.

The SDTT program is based on proven effective training protocols, and an overhead harness will be used for safety. The physiotherapist will be present but will provide assistance only when occasionally required. The SDTT+ anteroposterior perturbations program will trigger reactive gait adaptations by accelerations and decelerations of one of the belts of a split-belt treadmill, while the SDTT+ multi-directional perturbations will add mediolateral perturbations induced by a sideward translation of the treadmill. If a participant indicates difficulty in completing the training, blocks will be shortened in duration rather than in number and breaks were lengthened. Physiotherapists will only personalize the training progression if needed by omitting or adding a challenge according to the participants' level of exertion.

Each SDTT program (control and intervention) will comprise 12 sessions of 30 minutes each. The SDTT+ anteroposterior perturbations (APP) program will trigger reactive gait adaptations by accelerations and decelerations of one of the belts of a split-belt treadmill. The VR SDTT+ is achieved by shifting the visual input horizontally in virtual reality (VR-SDTT+). The SDTT+VR+APP is achieved using a virtual urban street whereby virtual obstacles must be stepped over to avoid induced APP. All perturbation types have been previously applied by us without any adverse events in inactive older adults.

After each session, the self-rated walking quality and mental effort visual analogue scales will be recorded and used to track progression and help guide the supervising clinician in tailoring the difficulty of subsequent sessions.

## B. Speed-dependent treadmill single session protocol: details

### *Determining comfortable overground walking speed*

Before the treadmill training, at each first training session of each training week (i.e. the first training session of a set of three training sessions), a single 20-meter walk test will be performed. This test will identify comfortable walking speed (CS).

### *Single session protocol on treadmill*

The CS recorded above will be used to set the treadmill speed, in accordance with Figure 3.

Each training session consists of three walking training trials at speeds V1, V2 and V3, intermitted with recovery walking trials. V1 will always be 80% of the comfortable walking speed, whereas V2 and V3 will be determined as the percentage of CS that progresses across training sessions (see “Training progression” for more detail). Prior to the first training trial, between each training trial and at the end of the last trial participants will walk at 70% of CS, as warmup/recovery walking trials. The warmup/recovery trials will last 2.5 minutes, unless longer breaks are necessary for the participant to tolerate the protocol. During walking, participants will be encouraged to swing (unless they are holding the handrails in the new speed interval, see above).

**Figure 3.** Overview of a single session of the SDTT

[figure not shown]

### *Methods to ensure safety*

During the treadmill walking participants will wear an overhead safety harness which does not support the participant's weight during walking, but will prevent them from falling. Treadmill railings will be used only if needed and only during the first minute of speed intervals to adjust to the speed demands.

A physiotherapist/clinician will be present to monitor the participant fatigue and gait pattern but will not give any physical assistance during the walking.

If possible, the physiotherapist will aim for completion of the training protocol (i.e., the total treadmill walking duration will remain the same) for the participant but will ensure sufficient breaks are inserted to maintain safety for the participant. During these resting breaks the participant will be seated and is allowed to drink water and or eat some snacks. Frequency and duration of these breaks will be reported.

### **C. Training progression**

The challenge of the training is expected to increase with the performance of the participant, as every first training session of the week the comfortable overground walking speed is re-assessed. So within a week participants will walk based on the same comfortable walking speed, but across weeks the speed may increase.

In addition, the %CS is progressed for V2 and V3 and the duration of the walking training trials (V1,V2,V3) will be lengthened over training sessions (Table 3). Progression of the VR challenge will be automatic based on the participant's performance, and the perturbation challenge will be increased across sessions as well.

*Table 3. Progression of training speed and duration*

| Training session # | CS of session # | V1 | V2 | V3 | Training trial duration progression | Max training trial duration (full progression) |
|---------------------------|------------------------|-----------|-----------|-----------|--------------------------------------------|-------------------------------------------------------|
| 1                         | 1                      | 80% CS    | 85% CS    | 90% CS    | 5 min*                                     | 5 min                                                 |
| 2                         | 1                      | 80% CS    | 85% CS    | 90% CS    | +30 sec                                    | 5 min 30 sec                                          |
| 3                         | 1                      | 80% CS    | 90% CS    | 95% CS    | =                                          | 5 min 30 sec                                          |
| 4                         | 4                      | 80% CS    | 90% CS    | 95% CS    | +30 sec                                    | 6 min                                                 |
| 5                         | 4                      | 80% CS    | 95% CS    | 100% CS   | =                                          | 6 min                                                 |
| 6                         | 4                      | 80% CS    | 95% CS    | 100% CS   | +30 sec                                    | 6 min 30 sec                                          |
| 7                         | 7                      | 80% CS    | 100% CS   | 105% CS   | =                                          | 6 min 30 sec                                          |
| 8                         | 7                      | 80% CS    | 100% CS   | 105% CS   | + 30 sec                                   | 7 min                                                 |
| 9                         | 7                      | 80% CS    | 100% CS   | 110% CS   | =                                          | 7 min                                                 |
| 10                        | 10                     | 80% CS    | 100% CS   | 105% CS   | +30 sec                                    | 7 min 30 sec                                          |
| 11                        | 10                     | 80% CS    | 100% CS   | 105% CS   | =                                          | 7 min 30 sec                                          |

|    |    |        |         |         |          |       |
|----|----|--------|---------|---------|----------|-------|
| 12 | 10 | 80% CS | 100% CS | 110% CS | + 30 sec | 8 min |
|----|----|--------|---------|---------|----------|-------|

\* *Or maximum tolerated duration*

